#### Plans to promote participant retention and complete follow-up {18b}

Retention for the assessment visits will be handled by the study staff. During informed consent, the staff will discuss with the participants the differences between intervention and assessment as well as the impact of dropout on the validity of study results, while also highlighting voluntary participation. For participants who drop out of the intervention (defined as nonattendance of the coaching or health education calls from that point to the end of the intervention period), we will continue to attempt to obtain outcome assessments. We will respond with empathy and attempt to collect primary outcomes if the full assessment is not feasible. Monetary incentives include payment for each study component and a $40 bonus for the completion of all sleep and ABPM time points.

#### Data management {19}

This study will use the secure, web-based Research Electronic Data Capture (REDCap) for data input. Case report forms will be designed to flag out-of-range values. When possible, participants will enter data directly into REDCap. For forms that need to be manually entered (e.g., blood test results, sleep apnea screening), data will be double-checked to verify accuracy. Intervention and control sessions will be stored on Box, a HIPAA-compliant file storage platform. Access to the study data will be limited to the investigators and staff with official roles relevant to the study data.

#### Confidentiality {27}

All investigators and staff will have up-to-date certification on confidentiality and privacy throughout the Collaborative Institutional Training Initiative (CITI) and will have completed additional HIPAA training through The University of Utah. Physical documents will be kept in folders within locked file cabinets in a locked office. Digital documents will be kept on a HIPAA-compliant Box drive or within REDCap. After the trial, data will be kept for 7 years following the last publication of the data. Names and other identifiable information will not be associated with study data. Participants will be assigned a screening ID number and when enrolled into the study, an individual trial ID number.

#### Plans for collection, laboratory evaluation and storage of biological specimens for genetic or molecular analysis in this trial/future use {33}

We will collect and store serum for targeted metabolomics analyses to evaluate whether changes in sleep affect biomarkers related to Alzheimer’s disease risk.

## Statistical methods

### Statistical methods for primary and secondary outcomes {20a}

The primary outcome of the proposed study is the change in the mean sleep duration from baseline to 8 weeks. The study sample size has been determined based on the primary analysis of covariance (ANCOVA) that will compare mean sleep duration at 8 weeks, with statistical adjustment for the baseline sleep duration and the sex and age randomization strata. The proposed ANCOVA approach is recommended for the evaluation of treatment effects on continuous outcomes in randomized trials because it optimally accounts for random imbalances in the outcome at baseline and regression to the mean, thus providing superior statistical power compared to the analyses of change scores or follow-up scores without adjustment for baseline levels [36].

The main secondary outcome for this study is the change in SBP from baseline to 8 weeks. Evaluation of the 24-h SBP outcome at 8 weeks will assure that few patients will have modified their antihypertensive medication regimen over the 8-week interval prior to the primary outcome assessment.

Evaluation of the 24-h SBP outcome at 8 weeks will assure that few patients will have modified their antihypertensive medication regimen over the 8-week interval prior to the primary outcome assessment. Similar ANCOVA models as used with sleep duration will also be used to evaluate the acute effects on this and other numeric secondary and tertiary outcomes.

We will use linear mixed models [37, 38] to analyze changes in sleep duration, BP measures, sleep, and other numeric tertiary outcomes over all follow-up visits, including the 8-week and 24-week assessments. These analyses will evaluate the persistence of treatment effects over the full 24-week follow-up period and will allow us to utilize all data collected (i.e., baseline, 8 weeks, and 24 weeks) while allowing for within-subject variation.

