### Trial design {8}

This is a single-blind, parallel-group, randomized controlled trial with a 1:1 allocation ratio and superiority framework. The study will test a behavioral sleep extension intervention compared to an education control group. The primary endpoint is 8 weeks and the secondary endpoint is 12 months. A CONSORT-style flow chart for the trial is shown in Fig. 1.

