### Eligibility criteria {10}

The following are the inclusion criteria:Age 18–65 years.In-office BP readings indicating elevated BP/stage I/II hypertension (SBP of 120–150 mmHg or DBP of 80–90 mmHg). Note that participants taking antihypertensive medications will be permitted if stable dose for > 8 weeks and willing to maintain their dose for the 8-week intervention period.Time in bed < 8 h and habitual sleep duration < 7 h via actigraphy at baseline/screening.Smartphone user.Able to read/write English.

The following are the exclusion criteria:High risk or presence of moderate to severe comorbid sleep disorders (i.e., obstructive sleep apnea, restless legs syndrome, or insomnia) as assessed by the questionnaires and overnight obstructive sleep apnea at the baseline/screeningResistant hypertension, defined as currently taking > 4 antihypertensive medications or 3 medications and standardized in lab BP > 130 mmHg SBP or 80 mmHg DBP at screeningHistory of cognitive or neurological disorders (e.g., dementia, Parkinson’s, multiple sclerosis)Arm circumference > 50 cmPresence of major psychiatric disorders (e.g., schizophrenia, bipolar disorder), alcohol abuse on screening questionnaire (women > 7 drinks per week and more than 4 drinks on one occasion; men > 14 drinks in 1 week and more than 5 on one occasion), drug use on the NIDA-Modified ASSIST (score > 3), and moderate to severe depressive symptoms (PHQ-8 > 9)Unstable or serious medical illness that would interfere with participation (cancer, renal disease on dialysis)Overnight work of more than 1 × per monthUse of hypnotic or stimulant medicationsSituations that would significantly impact the ability to extend sleep, including overnight caregiving responsibility for children under the age 1 and elderly or disabled adults > 1 × per weekInability to read or write in EnglishPregnancy/desire to become pregnant during the study periodCurrently following weight loss program, bariatric surgery in the past year, or current use of weight loss medications

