### Sample size {14}

Our power calculations are based on the assumption that the standard deviation (SD) for change in sleep duration from baseline to 8 weeks will not exceed 37.4 min, which is 10% higher than the SD for change in sleep duration of 34 min reported after 40 days in our previous study [22]. We also assume the Pearson correlation between baseline and follow-up sleep duration will not exceed 0.75, and that the attrition rate will not exceed 20%. Under these assumptions, 120 randomized participants (60 in each of the treatment and control groups) will provide at least 80% power with 2-sided *α* = 0.05 to detect a treatment effect of 20.2 min.

If we also assume that (1) the SD for baseline SBP will be $$\le$$ 11.8 mmHg, which is 10% higher than the average baseline SD reported in two previous studies [refs]; (2) the Pearson correlation between the baseline and 8-week follow-up SBP values will be $$\ge$$ 0.70; and (3) the attrition will be $$\le$$ 20%, and the sample size of 60 patients per treatment group will additionally ensure at least 80% power for the main secondary analysis to detect a treatment effect on the change in SBP of 4.86 mmHg.

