### Assignment of interventions: allocation

#### Sequence generation {16a}

Randomization will be performed using random permuted blocks with stratification by sex and antihypertensive medication use.

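### The allocation section and the primary ANCOVA name different second randomisation strata (antihypertensive medication use versus age), so the pre-specified covariate set contradicts the stated randomisation

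*Protocol article*

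**What the plan says.** Sequence generation {16a} fixes the allocation method: "Randomization will be performed using random permuted blocks with stratification by sex and antihypertensive medication use".

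Statistical methods for primary and secondary outcomes {20a} defines the primary analysis as an ANCOVA of mean sleep duration at 8 weeks, "with statistical adjustment for the baseline sleep duration and the sex and age randomization strata". For 24-h SBP and the other numeric outcomes the same section adds (last word of the sentence left off): "Similar ANCOVA models as used with sleep duration will also be used to evaluate the acute effects on this and other numeric secondary and tertiary".

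Three other places bear on the point:

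- Eligibility criteria {10} gives age only as a range, "Age 18–65 years". Recruitment {15} uses age only as an initial screening criterion. No section defines age bands.
- Eligibility criteria {10} says that "participants taking antihypertensive medications will be permitted if stable dose for > 8 weeks", so both levels of a medication stratum can be populated.
- Who will be blinded {17a} says that the statistician who prepares the randomisation table and carries out the analyses is not blinded.

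**The concern.** Both sections describe the strata of the same randomisation. They agree on sex and disagree on the second factor, so at least one is wrong. The protocol does not leave the covariates to another document. It states them, and they do not match its own allocation section.

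The main stake is pre-specification. As written, an analyst could fit continuous age, age in bands of his or her own making, medication use in place of age, or both. Any of these could be defended from some part of the article. That freedom sits in the primary model and is held by someone who knows the allocation. It extends to the main secondary outcome through the similar models.

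The lesser stake is efficiency. If the allocation was balanced on medication use and the model omits it, the variance between medication groups stays in the error term although the design has removed it from the treatment contrast. The reported standard error is then too large to the extent that medication use predicts the outcome.

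**Working it through.** **1. The sections side by side**

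| Item | Sequence generation {16a} | Statistical methods {20a} |
|---|---|---|
| First stratum | sex | sex |
| Second stratum | antihypertensive medication use | age |
| Levels of the second stratum | use (implicitly yes/no) | none given |

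**2. The plan's own figures**

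Inputs from Sample size {14}: the SD of change "will not exceed 37.4 min, which is 10% higher than the SD for change in sleep duration of 34 min"; "the Pearson correlation between baseline and follow-up sleep duration will not exceed 0.75"; attrition of at most 20%; 60 per arm; two-sided α = 0.05; 80% power. Trial design {8} describes a "randomized controlled trial with a 1:1 allocation ratio and superiority framework".

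- Evaluable per arm: 60 × 0.8 = 48.
- ANCOVA residual SD for sleep: 37.4 × √((1 + 0.75)/2) = 34.98 min.
- Detectable effect, normal approximation: (1.960 + 0.842) × 34.98 × √(2/48) = 20.0 min. The noncentral t gives 20.2 min, the stated figure.
- Residual SD for SBP: 11.8 × √(1 − 0.70²) = 8.43 mmHg. Detectable effect: 4.82 mmHg (normal) and 4.87 mmHg (noncentral t), against the stated 4.86.

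With 2 to 5 model parameters, the noncentral-t detectable effect is 20.21 to 20.22 min and stays at 4.87 mmHg. One stratum term more or less does not move the sample size.

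**3. Cost if medication use is the true stratum and is omitted**

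The documents do not say how much outcome variance medication use explains after the baseline value. Call that share R² and **assume** 2%, 5% and 10%. With exact balance, the true standard error is √(1 − R²) times the one that the omitting model reports. Hence:

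- True type I error when omitted = 2 × (1 − Φ(1.960/√(1 − R²)))
- Power when omitted = Φ(0.8416/√(1 − R²))
- Power when included = Φ(2.8016/√(1 − R²) − 1.960)

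| Assumed R² | Type I error, omitted | Power, omitted | Power, included | Forgone |
|---|---|---|---|---|
| 0% | 5.0% | 80.0% | 80.0% | 0 |
| 2% | 4.8% | 80.24% | 80.79% | 0.5 points |
| 5% | 4.4% | 80.61% | 81.97% | 1.4 points |
| 10% | 3.9% | 81.25% | 83.97% | 2.7 points |

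The last column is taken before rounding. If each power is first rounded to one decimal, the differences read 0.6, 1.4 and 2.8.

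**4. Simulation check**

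20,000 runs per setting, 48 per arm, half of each arm on medication (assumed), exact balance. Each pair is omitted versus included.

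| Assumed R² | Type I error | Power, sleep |
|---|---|---|
| 0% | 0.050 vs 0.050 | 0.80 vs 0.80 |
| 5% | 0.042 vs 0.047 | 0.81 vs 0.82 |
| 10% | 0.041 vs 0.052 | 0.81 vs 0.84 |
| 20% | 0.028 vs 0.051 | 0.83 vs 0.88 |

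SBP power behaves the same way (0.81 vs 0.84 at 10%). The simulation agrees with the formulas in direction and approximate size.

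**The case against.** The best case on the other side is that this is a one-word slip with little numerical consequence. Much of that stands. Omission makes the test conservative, power without the term stays at or above the planned 80%, and the treatment estimate is unbiased under randomisation. The variance shares are assumed. Nothing in the article indicates that medication use predicts actigraphic sleep duration once baseline sleep is in the model, so a share near zero is plausible for the primary outcome. Sex and age in the stated model could also absorb part of any medication effect.

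Three stronger readings are tempting and are not supported:

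- *The age stratum does not exist, so the model cannot be fitted.* The article cannot show which section has the slip. A model with sex and age can be fitted once a form for age is chosen. What is missing is that form, and agreement with the allocation section.
- *Medication use is the covariate that matters most for 24-h SBP.* No figure supports this. The SBP model would presumably adjust for baseline SBP, with an assumed correlation of at least 0.70. Participants are asked to keep medication constant if possible through week 8, so baseline may already carry much of the effect. The SBP models are also only described as similar, which does not fix their covariates.
- *The trial is mis-sized or its type I error is inflated.* The calculations show neither.

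The objection does not remove the contradiction. Nothing else in the article reconciles the two sections.

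**Conclusion.** The point holds as an internal contradiction about the second randomisation stratum, located in the definition of the primary model. The allocation section is the natural place to look for the true strata, but the article alone does not settle it.

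The weight rests on the ambiguous covariate set in an analysis run by an unblinded statistician, not on lost power. If medication use is the true stratum and is omitted, the test is slightly conservative, by the amounts tabulated above. Those amounts depend on assumed variance shares and on near-exact balance within strata, and they vanish as the share approaches zero. The sample size of 120 and the detectable effects of 20.2 min and 4.86 mmHg stand.

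**What to change.** Before outcome analysis, check the allocation table loaded in REDCap, make sections {16a} and {20a} name the same strata, and date the correction.

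- **If the table uses sex and medication use:** state in {20a} that the ANCOVA adjusts for the baseline value of the outcome, sex and antihypertensive medication use (yes/no), for sleep duration and for 24-h SBP. Age may stay, if wanted, as a pre-specified continuous covariate, but should not be called a stratum.
- **If the table uses sex and age:** correct {16a} and state the age bands used in the allocation.

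The cost is about one sentence. Section {16c} already has staff enter the stratification information in REDCap for each participant, so no new data are needed and the sample size does not change.

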**Methods:**

This is a single-blind, randomized controlled trial to determine the impact of a behavioral sleep extension intervention on sleep duration and cardiometabolic health among individuals with short sleep duration (< 7 h per night) and elevated blood pressure or hypertension (SBP 120–150 mmHg or DBP 80–90 mmHg). After completing the screening, participants will be randomly assigned to either a sleep coaching (intervention) or health education (control) group. The participants will have weekly contact for either coaching or education for 8 weeks (intervention period) followed by monthly coaching or education for the next 2 months (maintenance period). Participants will complete assessment visits, actigraphy, and 24-h ambulatory blood pressure recording at baseline/screening, 8 weeks, and 6 and 12 months. The primary outcome is sleep duration at 8 weeks, and the secondary outcome is blood pressure at 8 weeks.

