### Objectives {7}

The goal of this proposed study is to conduct a randomized controlled trial to test the efficacy of our behavioral sleep extension intervention on 24-h ambulatory BP (ABP) and other key biological and behavioral CMD risk factors among participants with short sleep duration and elevated BP/hypertension. The intervention will be completed over a 12-month period in 3 phases, intervention (weeks 0–8), maintenance (months 2–6), and follow-up (months 6–12), allowing us to test the short-term and extended effects of our intervention.Aim 1: To estimate the magnitude of the acute (8 weeks) and extended (12 months) effects of our behavioral sleep extension intervention compared to a health education control group on sleep durationAim 2: To test the effects of our behavioral sleep extension intervention compared with a health education control group on CMD risk factors including 24-h ABP, BMI, body fat, and CMD risk biomarkers (inflammation, glycemic control, lipids)Aim 3: To evaluate the effects of the intervention on key lifestyle behaviors (e.g., diet and physical activity) and patient-reported outcomes (sleep quality, sleepiness quality of life)

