##### Outcome measures

Primary outcome: Sleep duration at 8 weeks. Sleep will be measured by 8–10 days of actigraphy at baseline/screening, week 8, and 6 and 12 months with the Actiwatch Spectrum device (Philips Respironics Inc.). Devices will be configured using default settings and scored using the Acitware Software (Philips Respironics, Inc.). Actigraphy will be manually scored using a standardized procedure [16]. Participants will be provided with verbal and written instructions. Participants will wear the Actiwatches for 8–10 days in order to maximize the possibility of collecting 7 nights. Data will be considered valid if there are at least 5 nights. After the watches are retrieved, the research staff will use the Actiware software program to calculate the following variables: total sleep time, sleep onset time, sleep offset time, sleep duration, sleep efficiency, sleep latency, wake after sleep onset, and sleep fragmentation index. The staff will be trained on the scoring of actigraphy using a standardized procedure of readings, hands on practice/demonstration, and recorded presentations. Scored of each study file is reviewed by study PI [name] for scoring quality.

Main secondary outcome: 24-h SBP at 8 weeks. We will use the validated (AAMI criteria) SpaceLabs 90,207 monitor which is generally considered the “gold standard” for ABPM [25, 26]. ABPM for 24 h will be conducted at baseline/screening, 8 weeks, and 6 and 12 months follow-up. At each of the three 24-h ABPM assessments, the proper BP cuff size will be determined by measuring each participant’s arm circumference at the mid-point between the acromion and olecranon. Next, the monitor will be initialized, and the participant will be fitted with a SpaceLabs 90,207 monitor. Participants are instructed to hold their arm still (by their side or with their forearm resting on a desk/table when seated) when a reading is being taken. Each participant will be instructed by the study coordinator to try to keep their arm still and in the neutral position (which will be demonstrated for the participant prior to leaving the visit) from the time that she or he feels the arm cuff begin to inflate until it is fully deflated. The study staff is trained on ABPM procedures by 1:1 demonstration and practice with [name], study co-I. After demonstrating the ability to place the ABPM and instruct participants appropriately, the staff members are approved to conduct this study assessment.

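### The mixed-model text ends follow-up at 24 weeks, which contradicts the 12-month secondary endpoint, and no stated analysis names month 12

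*Protocol article*

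**What the plan says.** All references are to the protocol article.

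- **Trial design {8}:** "The primary endpoint is 8 weeks and the secondary endpoint is 12 months".
- **Objectives {7}:** Aim 1 covers the acute effect at 8 weeks and the "extended (12 months) effects of our behavioral sleep extension intervention" on sleep duration.
- **Hypotheses:** the benefit is expected to be still present, though smaller, at 12 months.
- **Outcomes {12} and Outcome measures:** actigraphy and ambulatory pressure are scheduled at baseline, week 8, month 6 and month 12. Changes to 6 and 12 months in sleep duration, 24-h systolic pressure and 24-h diastolic pressure fall under the other secondary outcomes. The main secondary outcome is 24-h systolic pressure at 8 weeks.
- **Statistical methods {20a}, ANCOVA:** the primary model compares arms at 8 weeks. Similar models "will also be used to evaluate the acute effects on this and other numeric secondary and tertiary outcomes".
- **Statistical methods {20a}, mixed model:** it is applied "over all follow-up visits, including the 8-week and 24-week assessments". The next sentence reads "These analyses will evaluate the persistence of treatment effects over the full 24-week follow-up period", and goes on to say that the analyses "will allow us to utilize all data collected (i.e., baseline, 8 weeks, and 24 weeks").

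**The concern.** The mixed model is the only method in the article that looks beyond 8 weeks. Its description gives a follow-up length and a visit list that stop at about half of the stated follow-up. An analyst who followed that list would not estimate the effect at the time point that Trial design {8} calls the secondary endpoint. Aim 1's extended effect and the 12-month hypothesis would then go unanswered.

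Month 12 matters for a second reason. Participant timeline {13} says that no intervention is delivered in months 6 to 12. The 12-month visit is thus the only actigraphy and ambulatory pressure assessment that shows what remains after coaching has stopped. If the text stays as it is, the form of the 12-month comparison is also open to choice after the data have been seen.

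**Working it through.** **1. The plan's own figure.** Sample size {14} gives an SD of change of 37.4 min, a correlation of 0.75, attrition of 20%, a difference of 20.2 min, two-sided α of 0.05 and 80% power. I assume the same SD at both visits.

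- SD at one visit: 37.4 / √(2 × (1 − 0.75)) = 52.9 min
- ANCOVA residual SD: 52.9 × √(1 − 0.75²) = 34.98 min
- Evaluable per arm: 2 × (1.960 + 0.842)² × 34.98² / 20.2² = 47.1, rounded up to 48
- Randomized per arm: 48 / (1 − 0.20) = 60, so 120 in total, as stated

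Power with 48 per arm is 80.7% by the normal approximation and 79.9% by the noncentral t. The systolic figure also reproduces: the residual SD is 11.8 × √(1 − 0.70²) = 8.43 mmHg, and power at 4.86 mmHg is 80.7% (normal) or 79.9% (t). Both calculations concern 8 weeks, so nothing said here about month 12 changes them.

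**2. The visit lists side by side.**

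| Source | Baseline | 8 weeks | 24 weeks / 6 months | 12 months |
|---|---|---|---|---|
| Abstract; Outcomes {12}; Outcome measures | yes | yes | yes | yes |
| Trial design {8}, endpoints | – | primary | – | secondary |
| Aim 1, Objectives {7} | – | acute | – | extended |
| Statistical methods {20a}, ANCOVA | covariate | yes | no | no |
| Statistical methods {20a}, mixed model as listed | yes | yes | yes | no |

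**3. Can 24 weeks stand for 12 months?** 24 × 7 / 30.44 = 5.5 months, and 12 months is 365.25 / 7 = 52.2 weeks. The 24-week label fits the 6-month visit but cannot mean the 12-month one.

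**4. Does another section supply the analysis?** Additional analyses {20b} describes per-protocol, responder and sleep-apnea moderator analyses, and the only follow-up time it names is 8 weeks. The missing-data section {20c} names no visit. No interim analysis is planned. Month 12 is therefore named in the aims, hypotheses, outcomes and schedule, but in no analysis.

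**5. Size.** At the planned attrition, 120 × (1 − 0.20) = 96 participants would have month-12 data. The 20% was set for the 8-week calculation, and the article gives no rate for month 12. The ceiling with no loss is 120. An assumed 30% loss would leave 120 × 0.70 = 84.

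**6. Two smaller slips.**

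- Outcome measures says "At each of the three 24-h ABPM assessments", although the sentence before it lists four time points. This could come from the same older schedule, but that is an inference.
- The Abstract has the eight weekly contacts "followed by monthly coaching or education for the next 2 months (maintenance period"), which ends near month 4 (1.8 + 2 = 3.8). Objectives {7}, Participant timeline {13} and Intervention description {11a} put maintenance at months 2 to 6. An end near month 4 matches neither 24 weeks nor 12 months, so this is a separate inconsistency with no bearing on whether month 12 is analysed.

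**The case against.** The strongest reply is that the article does contain a method for month 12. The sentence introducing the mixed model reaches "over all follow-up visits, including the 8-week and 24-week assessments". The word including need not be exhaustive, and 12-month changes are listed as secondary outcomes. On this view only the visit list is out of date. Much of this stands: a reader might infer that the investigators chose to discard the last wave, or that the extended aim has no method at all, and the documents support neither. The reply does not remove the contradiction. The next sentence calls 24 weeks the full period and introduces its list with i.e., which defines the data instead of giving examples.

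A second reply is that a separate analysis plan may settle the matter. That would answer an omission. Here the article states a follow-up length and a data set that conflict with its own design section.

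A third reply is that little is at stake, because the primary outcome, the main secondary outcome and the power calculation all concern 8 weeks. This is right, and it limits the point to the later outcomes.

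A reader might also infer that durability will be overstated, or try to size the harm by averaging assumed effects over the two modelled visits. The documents do not support either step. Section {20a} labels its period as 24 weeks, and no section says that visit effects will be averaged.

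**Conclusion.** The contradiction is real and sits within one document. Section {20a} sends the mixed model to all follow-up visits and then defines follow-up and data so that month 12 falls outside. No stated analysis names month 12, although it is the secondary endpoint in time, half of Aim 1 and part of the hypothesis. Taken literally, the list omits one of three post-baseline actigraphy and ambulatory pressure waves. That is about 96 participants, on the assumption that the 20% attrition set for 8 weeks also holds at 12 months. The likeliest explanation is text left from a 24-week schedule, but the article does not say so. The 8-week primary analysis, the main secondary analysis and the sample size stand as they are.

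**What to change.** In Statistical methods {20a}:

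- Replace the visit list with baseline, 8 weeks, 6 months and 12 months, and give the follow-up length as 12 months.
- State that the mixed model will estimate the between-arm difference at 12 months, and at 6 months, for sleep duration, 24-h systolic pressure and 24-h diastolic pressure.
- Label these as other secondary outcomes, with 24-h systolic pressure at 8 weeks kept as the main secondary outcome. The outcomes need naming because Trial design {8} uses the term secondary endpoint for a time point, not a variable.

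Arm-by-visit terms with categorical time would be a suitable way to obtain these contrasts. The remaining model detail can stay with the analysis plan.

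In Outcome measures, change the count of ambulatory assessments from three to four. Separately, reconcile the Abstract's maintenance length with Objectives {7}, Participant timeline {13} and Intervention description {11a}.

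The cost is wording only, since the 12-month data are already scheduled. The change should be made before any 12-month comparison is run.
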